### 8.2.3 Post-surgical Management of Close or Positive Margins

Re-resections are strongly recommended in order to achieve adequate resection margins and to avoid a multimodal treatment.

*Close/positive margins:* Close/positive margins are defined to be between 0 mm to <0.5 mm (Tis) and 0 mm to <1 mm (T1a) of distance between the tumor front and the surgical cut in the primary specimen. In this case a re-resection with an attempt to clear this margin should be performed, unless the patient refuses or has other adverse features requiring postoperative radiation therapy only. If this second margin shows no evidence of disease, the final margin is considered to be clear.

In case of inadequate resection margins despite of surgical efforts or if the patient refuses further surgery, an **adjuvant radiotherapy** shall be considered at the discretion of the institutional tumorboard and started within 5-6 weeks after surgery or re-resection, respectively. The technical details of the adjuvant radiotherapy are out of the scope of this study. The treatment planning and the conduction of the adjuvant radiotherapy must be carried out according to the institutional local standards. However, it is not allowed to use a fraction dose lower than 1.8 Gy or higher than 2.25 Gy, and a total dose lower than 60 Gy.

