#### **8.5 Data Collection and Follow-up for withdrawn participants**

Participants withdrawn from the trial before any treatment will undergo surgery or radiotherapy as planned by the tumor board. Patients may change their mind and prefer a treatment other than the study arm they were randomized to, or no treatment at all.

If a patient is withdrawn during or after the commencement of any study treatment, he/she will be asked, whether their study-specific data collected so far may be used. The data will be anonymized after the analysis.

A patient may also be withdrawn from the study by the local principal investigator, if the patient's participation in the study deemed to bear any additional risk for the well-being of the participant.

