#### **11.3.1 Datasets to be analyzed, analysis populations**

The primary analysis will follow the intention-to-treat (ITT) principle, i.e. all patients will be analyzed in the group they were originally assigned to at randomization regardless of any protocol violation.

In the per-protocol (PP) analysis, only patients that adhered to the protocol will be evaluated. Patients not receiving the allocated treatment or violating any of the inclusion criteria will be excluded from this analysis set.

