#### **11.3.2 Primary Analysis**

The primary analysis will be based on the ITT patient set. Patient characteristics will be presented in a table, separate by treatment group, as number and percentage, mean and standard deviation, or median and interquartile range, as appropriate.

VHI collected over 24 months will be analyzed using a repeated-measures, linear mixed-effects model with a random intercept for the patients and fixed effects for the baseline value, the treatment group, the time points (categorical), interaction terms between treatment group and time points, and randomization stratification factors. We will present the mean VHI difference between the two groups with associated 95% confidence intervals and p-values over all time points (primary outcome) as well as separate for each time point (secondary outcomes) from this model.

JS, GNE, and SPR are measured on a continuous scale and, therefore, will be analyzed using the same approach as for VHI. Jitter and shimmer are expected to show a log-normal distribution and will therefore be log-transformed before the analysis. If the distributions of the other two outcomes also severely deviate from a normal distribution, the measures will be transformed in an adequate way, e.g. by log-transformation. If normality cannot be achieved, measures will be analyzed using a non-parametric Wilcoxon rank sum test, separate for each time point.

Roughness, breathiness, and hoarseness are each assessed on an ordinal scale ranging from 0 to 3. These measures will be dichotomized into 2/3 versus 0/1 and analyzed using mixed-effects logistic regression with a random intercept for the patients and fixed effects for treatment group, the time points (categorical), interaction terms between treatment group and time points, and randomization stratification factors. We will present the odds ratio with associated 95% confidence intervals and p-values over all time points as well as separate for each time point from this model.

The time-to-event outcome loco-regional control will be evaluated using Kaplan-Meier curves and a Cox model adjusted for the randomization stratification factors.

Treatment toxicity at 2 and 5 years will be summarized descriptively for each group, showing the overall number of events as well as number and percentage of patients with events.

Patients will be censored for toxicity assessment at the time of loco-regional and/or distant tumor recurrence.

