### **11.3.3 Secondary Analyses**

In a secondary analysis, we will analyze all outcomes using the PP patient set. Moreover, we will perform subgroup analyses according to tumor stage (stage 0 vs. I), and VHI at baseline (<34 vs. ≥34).

For RBH, we will also consider a proportional odds logistic regression of the original ordinal outcome. Since the assessment is qualitative and performed by different raters, we will also test for heterogeneity between the raters and include a random intercept for raters in logistic models, if necessary.

Toxicities in both arms will be described and compared with TAME methodology.

Further secondary analyses may be described in the SAP.

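### Toxicity is planned only by assigned arm (ITT) and in the per-protocol set, so switchers' events are misplaced or lost and surgery-arm patients given adjuvant radiotherapy are not shown separately

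*Protocol*

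**What the plan says.** Protocol section 11.3.1 defines two analysis sets.

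- **ITT:** "all patients will be analyzed in the group they were originally assigned to at randomization regardless of any protocol violation".
- **PP:** "Patients not receiving the allocated treatment or violating any of the inclusion criteria will be excluded from this analysis set".

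Section 11.3.2 opens with "The primary analysis will be based on the ITT patient set" and later states: "Treatment toxicity at 2 and 5 years will be summarized descriptively for each group". It also censors toxicity assessment at recurrence. Section 11.3.3 adds "In a secondary analysis, we will analyze all outcomes using the PP patient set" and "Toxicities in both arms will be described and compared with TAME". The TAME sentence names no analysis set.

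Other sections foresee patients whose treatment differs from, or goes beyond, the label of their arm:

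- Section 8.5: "Patients may change their mind and prefer a treatment other than the study arm they were randomized to, or no treatment at all".
- Section 8.2.3: for Arm A patients whose margins stay inadequate or who decline further surgery, adjuvant radiotherapy "shall be considered at the discretion of the institutional tumorboard and started within 5-6 weeks after surgery or re-resection, respectively". It follows local standards, and its technique lies outside the study's scope.
- Section 8.2.1: patients whom the anaesthesia team declines are withdrawn and treated outside the protocol. This can arise only in Arm A.

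**The concern.** Toxicity is both a secondary and a safety objective (sections 4.3 and 4.4), and section 8.1 gives safety the same weight as efficacy for both interventions. Readers will use the toxicity table in two ways: to compare the strategies of starting with surgery or with irradiation, and to learn what each treatment does to a patient. The ITT table answers the first question. Neither planned table fully answers the second.

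Under ITT, a patient assigned to TLM but irradiated instead brings radiation effects into the TLM column, and an untreated patient dilutes the arm's percentage. Under PP, the switcher's events disappear. A patient who had TLM and then adjuvant radiotherapy did receive the allocated treatment, so the stated PP exclusions do not remove that patient. Any radiation effects then sit in the TLM column in both tables with nothing to mark them. In a trial this small, a few such patients can visibly change a percentage.

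**Working it through.** **Which set catches which patient**

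| Patient | ITT table | PP table |
|---|---|---|
| Assigned TLM, had TLM only | TLM | TLM |
| Assigned TLM, had TLM then adjuvant radiotherapy | TLM, unmarked | TLM, unmarked |
| Assigned TLM, irradiated instead, still followed | TLM | removed |
| Assigned SVCI, operated instead, still followed | SVCI | removed |
| Assigned either arm, untreated, still followed | assigned arm | removed |

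Radiotherapy given for recurrence does not enter, because toxicity is censored at that point.

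**Arm size.** Section 11.1 assumes a difference of 8 VHI points, a standard deviation of 8, two-sided alpha 0.05 and 80% power, and gives 17 per group. The noncentral t calculation gives power 78.1% at 16 per arm and 80.7% at 17, so 17 per arm (34 in total) is reproduced.

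**Weight of one patient.** 1/17 = 5.9 percentage points of an arm, 2/17 = 11.8 and 3/17 = 17.6. These are ceilings on the shift in the TLM percentage: they apply only if each such patient has an event that would not otherwise have occurred.

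**Expected effect on the comparison.** Let p_S be the risk of a given toxicity after surgery alone and p_R the risk in Arm B. Assume that k of 17 Arm A patients are irradiated before any recurrence and then carry p_R. The Arm A rate is

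[(17 − k)·p_S + k·p_R] / 17,

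so the difference by arm is

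p_R − Arm A rate = (p_R − p_S)·(1 − k/17).

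The relative shrinkage is k/17 whatever the two risks are: 5.9% for k = 1, 11.8% for k = 2 and 17.6% for k = 3.

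The protocol gives neither risk nor k. With assumed risks:

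| p_S, p_R (assumed) | k = 0 | k = 1 | k = 2 | k = 3 |
|---|---|---|---|---|
| 10%, 30% | 20.0 points | 18.8 | 17.6 | 16.5 |
| 10%, 50% | 40.0 points | 37.6 | 35.3 | 32.9 |

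In absolute terms that is a loss of 1.2 to 3.5 points in the first row and 2.4 to 7.1 in the second.

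**What the equal-risk assumption hides.** Adjuvant radiotherapy in Arm A need not be SVCI, and it follows surgery. Its risk could be higher or lower than p_R, and the shrinkage would change with it.

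**The case against.** Four points can be made for the plan as written, and each has some force.

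- **Adjuvant radiotherapy belongs to Arm A.** Section 8.2.3 makes it a step of the surgical strategy, Table 2 lists it among the possible risks of TLM, and the objectives compare toxicity by study arm. A reader might infer that counting it in Arm A is an error. It is not. Taking those patients out would remove a real cost of choosing surgery and would condition on margin status or on refusal of re-resection, both of which arise after randomisation. What remains is that the table cannot show how much of Arm A's toxicity came with radiotherapy.
- **PP already compares treated with treated.** Because patients who did not receive the allocated treatment are excluded, the PP label equals the primary treatment received. This stands. But PP discards the switchers' events and still does not separate TLM with adjuvant radiotherapy from TLM alone.
- **Switchers may have no data.** Sections 7.5 and 8.5 make use of a withdrawn patient's data depend on permission, and a patient withdrawn before treatment may contribute no later toxicity at all. Regrouping cannot recover that. The switcher part of the point covers only those who stay in follow-up.
- **The SAP may add a safety set.** Section 11.3.3 leaves room for further secondary analyses there. The protocol is not silent, however: its populations section names two sets, and the next two sections apply them to toxicity.

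Two further inferences go too far. A shift of 6 to 18 points should not be read as expected, because it is a ceiling on assumed counts. Nor do the documents show that the Appendix A items are mainly radiation effects, since the list assigns none of them to one treatment.

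**Conclusion.** The point holds as a modest one about how a secondary and safety outcome is displayed. The stated analyses place toxicity in the ITT set and repeat it in PP, and neither shows toxicity by all treatment actually received. Switchers who remain in follow-up are counted under a treatment they did not have, or are dropped. TLM patients with adjuvant radiotherapy cannot be told apart from the rest of Arm A.

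The size cannot be fixed from the protocol. For one to three irradiated Arm A patients, the difference between arms shrinks by about 6% to 18% of its value. This rests on 17 analysed per arm, on assumed counts, and on the assumption that those patients carry the Arm B risk. That blurs the toxicity contrast; it does not erase it. The primary VHI analysis, for which ITT is the right basis, is not touched.

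**What to change.** 1. Add a safety set to section 11.3.1: all patients who started any study treatment and have toxicity follow-up, grouped by treatment received.
2. Use it in sections 11.3.2 and 11.3.3 for a toxicity table and a TAME display with three columns: TLM alone, TLM plus adjuvant radiotherapy, and SVCI. The three columns are needed because an as-treated set by itself would still leave adjuvant cases under TLM.
3. Keep the as-randomised table as the comparison of strategies, and state which set each TAME summary uses.
4. Report how many patients in each arm switched, went untreated, had adjuvant radiotherapy, or left without toxicity follow-up.

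The cost is one definition and one table layout. Surgical quality assurance (section 8.2.7.2) already checks re-resection and adjuvant radiotherapy after a positive margin, so much of the information should be on record. The sponsor should confirm that the eCRF also captures treatment received for switchers and for close-margin cases. The drawback is that the as-treated groups, and above all the split within TLM, depend on events after randomisation and are not protected by it. They should be labelled descriptive. Sample size, treatment and the primary analysis do not change.

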| Pregnancy test for women with child-bearing potential                                       | -28 – 0                                                      | 3 – 7 ‡                                                                             | until 3 rd month ‡                                                                                                     |
| Arm A: Transoral CO 2 -Laser Microsurgical Cordectomy ▽               |                                                              | day of surgery +/- day of re-resection                                                         |                                                                                                                                              |
| Arm B: Single Vocal Cord Irradiation ▽                                           |                                                              | 3 (16 fractions)                                                                               |                                                                                                                                              |

GNE: Glottal-to-Noise Excitation Ratio; JS: Jitter and Shimmer; RBH: Roughness – Breathiness – Hoarseness; SAEs: serious adverse events; SCCGL: squamous cell carcinoma of glottic larynx; SPR: Singing Power Ratio; VHI: voice handicap index

\*: Even if done on the same day, patient enrollment shall be done after the completion of the necessary documentation

#: VHI at 6 weeks after the end of treatment (regardless of study arm) will be assessed to evaluate the need for phoniatric rehabilitation, but not as a study-specific outcome measure (i.e. primary endpoint) to avoid lead time bias. Patients with a VHI > 14 will be recommended to undergo a phoniatric rehabilitation, but the examiner should not try to persuade the patient. Similarly, any VHI >14 at any follow-up time point or patients' request justifies the need for phoniatric rehabilitation, which will be recommended to the patients regardless of study arm. No need to record the VHI in the CRFs.

‡: The baseline toxicity scores and smoking status may be documented after the accrual but it must be done before the start of trial treatment.

‡: If clinically indicated

▽: The treatment shall start within 28 days post-accrual

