### 3. BACKGROUND AND RATIONALE

#### 3.1 Background and Rationale

Head and neck squamous cell carcinoma (HNSCC) is the 6th most common type of cancer worldwide. Of all head and neck cancers, approximately 30% originates from the larynx. In Europe, annually 52,000 patients are diagnosed with cancer of the larynx. About 50–60% of laryngeal squamous cell carcinomas arise from the glottic region and over 80% of these patients present in an early stage. The larynx has important roles in production of voice, coordination of deglutition, and respiration. Therefore, the treatment aim of laryngeal cancer is not only achievement of maximum disease control, but also maintenance of function. Transoral CO2-Laser Microsurgical Cordectomy (TLM) and radiotherapy are well-established standard treatment modalities for unilateral stage 0-I carcinoma in situ and squamous cell carcinoma of glottic larynx (for convenience, both will be mentioned as SCCGL throughout this protocol). Based on various clinical studies and meta-analyses, functional and oncological outcome (overall survival and local control) after both treatment modalities are comparable. However, no properly conducted randomized trials comparing these treatments exist. The only such trial with the endpoint of voice quality had to be prematurely closed due to low accrual.

The treatment option varies remarkably in different countries and among institutions. Especially in the case of unilateral SCCGL, other factors such as voice quality, cultural and socio-economic factors, and patients' preference should be considered. Hoarseness is one of the main and early signs of SCCGL, whereas both radiotherapy and TLM influence voice quality by altering the vocal cord motion and anatomy. Another issue worth to consider is the treatment time. Surgery is performed in one day followed by a few days of hospital stay. In contrast, radiotherapy is applied in daily fractions. Although each fraction only takes few minutes, the patients have to visit the radiation oncology department over a course of 4 to 7 weeks, depending on the institutional preference of dose and fractionation. The post-treatment follow-up schedules are identical for both strategies.

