#### 6.2.2 Blinding procedures

Due to obvious differences between surgery and radiotherapy, it is not possible to have a blinded design in this study setting.

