### **11.2 Randomization and Stratification**

A probabilistic minimization technique will be used for random treatment allocation between the two treatment arms using a 1:1 ratio. The computer chooses a treatment dynamically, based on the tumor stage (Stage 0 vs. I), and VHI at baseline (<34 vs. ≥34) as two predefined stratification factors.

Allocation will be done via a dedicated website within the clinical trial management system also containing the electronic case report forms. Only system administrators who are otherwise not involved in the trial will have access to the algorithm and stored lists during the recruitment period. Investigators receive the allocation only after registration of a patient. The underlying randomization lists and details of the minimization algorithm will not be disclosed but kept securely at CTU Bern. All these measures will help to ensure concealment of allocation.

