## 17. APPENDICES

### APPENDIX A: List of Possible Treatment-Related Toxicities (CTCAE v.5.0)

| Tissue/Organ               | Grade 1                                                                                                | Grade 2                                                                                                                                         | Grade 3                                                                                                                | Grade 4                                                                                             |
|----------------------------|--------------------------------------------------------------------------------------------------------|-------------------------------------------------------------------------------------------------------------------------------------------------|------------------------------------------------------------------------------------------------------------------------|-----------------------------------------------------------------------------------------------------|
| Skin Induration     | Mild induration, able to move skin parallel to plane (sliding) and perpendicular to skin (pinching up) | Moderate induration, able to slide skin, unable to pinch skin; instrumental ADL                                                                 | Severe induration, unable to slide skin; limiting joint movement or orifice (e.g. mouth, anus); limiting self-care ADL | Generalized; associated with signs or symptoms of impaired breathing or feeding                     |
| Skin Atrophy        | Covering <10% BSA; associated with telangiectasias or changes in skin color                            | Covering 10 - 30% BSA; associated with striae or adnexal structure loss                                                                         | Covering >30% BSA; associated with ulceration                                                                          | -                                                                                                   |

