| Dysphagia           | Symptomatic, able to eat regular diet                                                                  | Symptomatic and altered eating/swallowing                                                                                                       | Severely altered eating/swallowing; tube feeding or total parenteral nutrition or hospitalization indicated            | Life-threatening consequences; urgent intervention indicated                                        |
| Hoarseness          | Mild or intermittent voice change; fully understandable; self-resolves                                 | Moderate or persistent voice changes; may require occasional repetition but understandable on telephone; medical evaluation indicated           | Severe voice changes including predominantly whispered speech                                                          | -                                                                                                   |
| Laryngeal Stenosis  | Asymptomatic; clinical or diagnostic observations only; intervention not indicated                     | Symptomatic (e.g., noisy airway breathing), no respiratory distress; medical intervention indicated (e.g., steroids); limiting instrumental ADL | Limiting self-care ADL; stridor; endoscopic intervention indicated (e.g., stent, laser)                                | Life-threatening consequences; urgent intervention indicated                                        |
| Pharyngeal Stenosis | Asymptomatic; clinical or diagnostic observations only; intervention not indicated                     | Symptomatic (e.g., noisy airway breathing), no respiratory distress; medical intervention indicated (e.g., steroids); limiting instrumental ADL | Limiting self-care ADL; stridor; endoscopic intervention indicated (e.g., stent, laser)                                | Life-threatening airway compromise; urgent intervention indicated (e.g., tracheotomy or intubation) |

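### Baseline toxicity grades may be documented after allocation is known, and the toxicity summary makes no use of them, so residual pre-existing hoarseness can be counted as treatment toxicity

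*Protocol*

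**What the plan says.** **Summary rule.** Section 11.3.2 describes treatment toxicity at 2 and 5 years for each group, "showing the overall number of events as well as number and percentage of patients with events". It gives no grade threshold and no comparison with baseline. Section 11.3.3 adds a comparison of the arms by the TAME method, again without mentioning baseline.

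**Item concerned.** Appendix A lists hoarseness. Grade 1 is "Mild or intermittent voice change; fully understandable; self-resolves" and grade 2 is "Moderate or persistent voice changes; may require occasional repetition but understandable on telephone; medical evaluation indicated". Section 3.1 states: "Hoarseness is one of the main and early signs of SCCGL".

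**Timing of the baseline grade.** Table 1 (Study Schedule, repeated in Section 9.1) places baseline toxicity in the screening window, day -28 to 0. Its footnote then relaxes this: "The baseline toxicity scores and smoking status may be documented after the accrual but it must be done before the start of trial treatment".

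**Knowledge of the arm.** Section 11.2: "Investigators receive the allocation only after registration of a patient". Section 6.2.2: "it is not possible to have a blinded design in this study setting".

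**Limits on what is recorded.** Under Section 9.2.3, grade 1 and 2 events before the month-6 visit need not be reported. Under Sections 9.2.2 and 11.3.2, toxicity follow-up is censored at loco-regional or distant recurrence.

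**The concern.** There are two separate weaknesses.

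First, the count takes no account of where the patient started. A patient with grade 2 hoarseness before treatment and grade 2 at month 24 is counted like a patient who went from grade 0 to grade 2. The first has not been made worse, yet both can appear as treatment toxicity. The protocol collects the value needed to tell them apart and states no use for it.

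Second, the obvious remedy, counting only worsening over baseline, is only as good as the baseline. If that grade may be entered once the arm is known, a clinician-assigned score could be influenced by the allocation. This is a data-collection rule: once a grade has been obtained late, no analysis plan can restore a value from before allocation.

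Toxicity is a secondary outcome (Section 5.2) and a safety objective (Section 4.4). With 17 patients per arm, a few patients counted without having worsened change the reported percentage visibly.

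**Working it through.** **1. Plan's own figures.** The protocol gives no numerical target for toxicity. Its 17 patients per arm come from the primary outcome (difference 8, SD 8, two-sided alpha 0.05, power 80%). A two-sample t-test gives 16.7, rounded up to 17 per arm, with power 80.7%. That reproduces the stated 34, and 17 is used below only as a denominator.

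**2. Order of events at baseline.**
- Day -28 to 0: screening, with baseline toxicity nominally scheduled here.
- Registration: the investigator then receives the allocation (Section 11.2).
- Up to 28 days after accrual: treatment starts (Table 1 footnote; 4 weeks in Section 8.1).

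The footnote therefore leaves a window of up to 28 days in which a baseline grade can be documented with the arm known.

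**3. Comparison with the voice measures.** Baseline VHI, JS, RBH, GNE and SPR are inclusion criterion 3 (Section 7.1), and the phoniatric assessments must be complete before registration (Section 7.3). Toxicity is handled differently, and no reason is given.

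**4. Use of baseline in the analysis.** In Section 11.3.2 the VHI model has the baseline value as a fixed effect, and JS, GNE and SPR follow the same approach. The toxicity paragraph has no counterpart, and no other section says how the baseline grade is used.

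**5. Number of occasions.** Toxicity visits from month 6 to month 24 fall at 6, 9, 12, 15, 18, 21 and 24, which is 7. Visits at 30, 36, 42, 48, 54 and 60 add 6, which makes 13. The protocol does not say whether an unchanged finding is counted once or at each visit. If at each visit, one persisting hoarseness could enter the overall number of events up to 7 times by 2 years and 13 times by 5 years.

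**6. Illustration of size (all inputs assumed).** Let b be the share of patients with hoarseness of grade 1 or higher at baseline, r the share of those in whom it is still graded after month 6, and w the share with new or worsened hoarseness, independent of the first two.

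- Counted at any grade: b·r + w·(1 − b·r)
- Counted only if worse than baseline: w
- Excess: b·r·(1 − w)

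| b | r | w | Any grade, of 17 | Worse than baseline, of 17 | Excess, of 17 |
|---|---|---|---|---|---|
| 0.5 | 0.2 | 0.1 | 3.2 (19%) | 1.7 (10%) | 1.5 |
| 0.7 | 0.4 | 0.1 | 6.0 (35%) | 1.7 (10%) | 4.3 |
| 0.9 | 0.6 | 0.1 | 10.0 (59%) | 1.7 (10%) | 8.3 |

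The width of the range shows that the excess depends almost entirely on b and r, neither of which the protocol gives.

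**The case against.** **The event definition belongs in the SAP.** Section 11.3 announces a detailed SAP, which is not shown, and comparison with baseline is commonly specified there. This stands in part: the SAP may settle the counting rule, and the protocol's silence does not prove that improved or unchanged hoarseness will be counted. It does not reach the footnote, which governs data collection.

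**An unused baseline cannot bias anything.** Correct. Late documentation does no harm to the summary as written. It matters only once change from baseline is analysed, which is the natural repair of the first weakness.

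**Documented is not the same as scored.** Also correct. A grade could be assessed in screening and entered later. The footnote does not require that, however, so scoring after allocation is permitted though not stated.

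**Voice status is recorded before allocation anyway.** Baseline VHI and the RBH rating, which is to be assessed blind, are available. They are not CTCAE grades, though, and do not cover other Appendix A items such as dysphagia, pain or fatigue.

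**Stronger readings that a reader might infer.**
- *Tumour symptoms are reported as toxicity.* Not supported. Low-grade events need recording only from month 6, after the tumour has been treated, and recurrence censors. What can be counted is residual pre-existing hoarseness.
- *Nearly every patient will have an event.* No figure in the protocol supports this. Grade 1 hoarseness is also defined as self-resolving, which fits poorly with long persistence at that grade.
- *One arm is systematically favoured.* Minimization on baseline VHI (<34 vs. ≥34) and stage should limit imbalance in pre-existing voice impairment. Chance differences remain possible with 17 per arm, but the main effect is on both rates alike.

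**Conclusion.** The point holds in a limited form. The firmer part is the footnote: it allows baseline CTCAE grades to be documented when the allocation may already be known in an unblinded trial, whereas the baseline voice measures must be complete before registration. The second part is that Section 11.3.2 counts toxicity without reference to that baseline, so residual hoarseness from before treatment can be reported as treatment toxicity from month 6 onward.

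The expected consequence is inflated rates in both arms, not a systematic difference between them. The protocol does not allow the amount to be estimated; the 1.5 to 8.3 patients per arm above only illustrate assumed inputs. The primary outcome is unaffected. The change is worth making because it is specific and costs very little.

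**What to change.** 1. **Table 1 footnote (Study Schedule and Section 9.1).** Require baseline toxicity grades to be recorded before randomization, as the baseline voice measures already are.
2. **Sections 9.2.2 and 11.3.2.** State that a toxicity event is an Appendix A item whose CTCAE grade exceeds that patient's baseline grade, counted once per patient and item at the worst grade. This also settles the repeated-visit question.

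Reporting hoarseness separately from the overall toxicity figure is optional, since VHI and RBH already have their own analyses.

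**Cost.** Only wording changes. The baseline grades are already collected and scheduled in the screening window, so there is no new assessment. The small downside is that sites can no longer enter them after accrual.
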